## Abstract

**Background:**

Annually, some 9000 people in Switzerland suffer a first time stroke. Of these 60% are left with moderate to severe walking disability. Evidence shows that rehabilitation techniques which emphasise activity of the hemiplegic side increase ipsilesional cortical plasticity and improve functional outcomes. Canes are commonly used in gait rehabilitation although they significantly reduce hemiplegic muscle activity. We have shown that an orthosis "TheraTogs" (a corset with elasticated strapping) significantly increases hemiplegic muscle activity during gait. The aim of the present study is to investigate the long term effects on the recovery of gait, balance and social participation of gait rehabilitation with TheraTogs compared to gait rehabilitation with a cane following first time acute stroke.

**Methods/Design:**

Multi-centre, single blind, randomised trial with 120 patients after first stroke. When subjects have reached Functional Ambulation Category 3 they will be randomly allocated into TheraTogs or cane group. TheraTogs will be applied to support hip extensor and abductor musculature according to a standardised procedure. Cane walking held at the level of the radial styloid of the sound wrist. Subjects will walk throughout the day with only the assigned walking aid. Standard therapy treatments and usual care will remain unchanged and documented. The intervention will continue for five weeks or until patients have reached Functional Ambulation category 5. Outcome measures will be assessed the day before begin of intervention, the day after completion, 3 months, 6 months and 2 years. Primary outcome: Timed "up and go" test, secondary outcomes: peak surface EMG of gluteus maximus and gluteus medius, activation patterns of hemiplegic leg musculature, temporo-spatial gait parameters, hemiplegic hip kinematics in the frontal and sagittal planes, dynamic balance, daily activity measured by accelerometry, Stroke Impact Scale. Significance levels will be 5% with 95% CI's. IntentionToTreat analyses will be performed. Descriptive statistics will be presented.

**Discussion:**

This study could have significant implications for the clinical practice of gait rehabilitation after stroke, particularly the effect and appropriate use of walking aids.

The results could be important for the development of clinical guidelines and for the socio-economic costs of post-stroke care

**Trial registration number:**

ClinicalTrials.gov NCT01366729.

## Background - presentation of the hypothesis

Stroke is the leading cause of acquired disability in adults [1]. In Switzerland approximately 9000 people a year suffer a first time stroke [2]. Of those patients who survive the acute phase, between 20 and 30% are unable to walk [3]. Those who can are often left with moderate to severe walking disability and reduced gait speeds [3,4]. The risk of falling increases--a recent study indicating that at 3 months 28% of stroke patients have fallen [5]. The resulting disability has an enormous socioeconomic impact on patients, families and health service providers [6,7].

Rehabilitation methods which improve balance and gait are crucial for the quality of life of stroke victims and to reduce the ongoing cost of long term care. Studies have shown that early rehabilitation in specialised settings e.g. stroke units results in better functional outcome than in non-specialised units [8,9]. It has been suggested that these better results are achieved partly due to enhanced staff awareness of the importance of mobility thus preventing secondary complications such as loss of cardiovascular fitness or muscle weakness. The physical environment is also likely to be adapted enabling more independent movement [10,11]. Current rehabilitation methods which aim to improve motor control during walking do not appear to deliver additional improvements [12,13]. A recent meta-analysis showed that only cardiorespiratory physical fitness training provides robust evidence for a benefit to walking ability after stroke. Repetitive task training also appeared to have some effect. Motor and neurophysiological approaches did not demonstrate a positive effect on walking recovery [13]. This suggests that underlying mechanisms responsible for the recovery of motor co-ordination and control of walking following stroke are not significantly influenced by current therapy methods. These findings are further illustrated by studies which show that long term improvements in gait function occur in the absence of improvements in muscle co-ordination patterns [14] or improved kinematic or kinetic gait profiles [15]. Buurke et al. [14] concluded that "functional gait improvements may be more related to compensatory strategies than by restitution of muscle co-ordination patterns in the affected leg." Kautz et al. [16] concluded that "There is no evidence of improved locomotor co-ordination post intervention. The increased walking and pedalling speed were achieved by a more proficient use of the same impaired pattern without EMG timing changes, likely because of increased strength and endurance post intervention." We suggest that improvements in gait function due to current rehabilitation methods are predominantly achieved through more efficient use of abnormal movement patterns. This may be a reason for the generally low level of independence and function achieved following stroke.

Spontaneous recovery which occurs within the first weeks post stroke largely defines long term functional outcome [17]. Recent studies investigating changes in the cerebral cortex following focal injury have indicated that cortical plasticity and neuronal growth that occurs early after infarct may "underlie the brain's self-repair process" [18,19]. Evidence shows that this early cortical plasticity is an important factor in the spontaneous recovery of motor control which predicts long term outcome [18-22]. We suggest that it is this process which is inadequately influenced by current rehabilitation methods. The recovery of motor skills following stroke relies on the brains ability to reorganise its neuronal control of movement [19,20]. Reorganisation can occur within and between cortical networks both within the lesioned and non-lesioned hemisphere [18,21]. Rossini et al. stated that "Reorganization phenomena following ischemic stroke observed so far, may be classified into two main groups: overactivation of areas belonging to the neural network for a specific task--or activation of unusual areas that attempt to replace the function of the damaged tissue" [18]. The overactivation of the original neural network is primarily activity in the lesioned hemisphere. Following stroke cortical activity has been recorded in both lesioned and non-lesioned hemispheres during movement [21,23]. Increasingly findings show that increased activity in the lesioned hemisphere correlates with better recovery and improved motor performance [23-27]. Conversely increased activity in the contralesional hemisphere is associated with poorer motor recovery of the hemiplegic limb [26,27]. It appears that improved motor recovery occurs when the brain is able to make use of the original neural network to control movement. When new networks are formed for example in the unaffected hemisphere, motor recovery is reduced. The authors suggest that activity in the original network represents "true" recovery. The recruitment of new networks may represent the learning of compensatory movement strategies associated with poorer functional outcome.

Findings in favour of this hypothesis have been demonstrated in both upper and lower limbs [25-27]. As post-injury behavioural experience is critical to the reassembly of adaptive networks and strongly influences cortical reorganisation [22,28] these results indicate that treatment approaches which promote increased plasticity in the lesioned hemisphere will promote greater functional recovery. This assumption is supported by a recent meta-analysis [21] which examined whether participating in stroke rehabilitation which emphasised use of the paretic upper limb was associated with increased cortical activity of the lesioned hemisphere and consequently better function. The review concluded that neural changes in the sensorimotor cortex of the lesioned hemisphere were achieved with rehabilitation interventions that emphasized use of the paretic upper limb and resulted in improved functional motor gains.

Nudo et al. [28] demonstrated with squirrel monkeys that forced retraining of skilled hand use prevented loss of hand territory representation adjacent to the infarct and in some instances the representations expanded. This functional reorganization was accompanied by recovery of skilled hand movements. Control monkeys with identical lesions who did not receive therapy lost paretic hand representation und function.

In general these results suggest that therapies which emphasise use of the hemiplegic side promote plasticity in the lesioned hemisphere through emphasising the use of previously established neural networks and are associated with improved function. It may be that therapies which promote compensatory movement or reduce activity of the hemiplegic limb inhibit plasticity in the lesioned hemisphere and promote the development of new neural networks associated with reduced function.

To date therapies which emphasise use of the hemiplegic limb have been confined to the upper extremity [29,30] and have not been applied during gait rehabilitation following stroke. Canes are very commonly used post stroke although studies have consistently shown a significant reduction in surface electromyography (EMG) activity in all muscle groups on the side contralateral to cane use in both stroke and non-stroke patients [14,31-33]. In light of the factors which increase plastic reorganisation in the lesioned hemisphere, namely interventions which emphasise use of the paretic limb, the effect of canes which reduce activity in the hemiplegic side may be to inhibit activity in the original neural networks responsible for lower limb control resulting in poorer walking function.

In gait rehabilitation, attention should also be paid to the optimal restoration of balance. In relation to balance, evidence shows that balance control does not occur automatically at spinal cord and brainstem level as has previously been thought, but rather is highly influenced by cortical activity and cognitive control [34-36]. Two main types of balance strategies are recognised--fixed support or change of support strategies [34,35]. Fixed support strategies are used when no stepping or reaching activities are needed to maintain balance. Rotatory torques are generated through muscle activity primarily around the hip and ankle. Change of support strategies are used in challenging conditions when stepping or reaching reactions are necessary to maintain equilibrium. Fixed support strategies use less cognitive resources than change in support [34,35]. Elderly people or subjects with poor balance use more change in support strategies and therefore more cognitive resources than younger, healthy subjects to maintain equilibrium under the same conditions.

The authors suggest that balance rehabilitation should attempt to restore balance strategies used by healthy individuals--namely fixed support responses requiring fewer cognitive resources in unchallenging situations. However cane use increases the base of support when walking through use of the arms. This strategy may emphasise use of cortical networks used for reaching "change of support" reactions. It emphasises use of cognitive resources on safe level ground and reduces the use of "fixed support" strategies. The authors suggest this leads to a long term reduction of automatic balance responses. It may be that because cognitive resources are needed in safe, level environments fewer additional resources are available for more difficult conditions such as walking outside or on public transport. The long term effects of canes on balance recovery and functional gait following stroke has to our knowledge been investigated in one study [37]. Balance recovery and community participation were shown to be reduced.

Taking all of these considerations together, the authors suggest that an optimal walking aid for post stroke gait rehabilitation would provide enough support to enable independent early walking without reducing hemiplegic muscle activity or inhibiting the use of balance reactions. The immediate effect of an elasticised orthotic walking aid (TheraTogs) on hemiplegic hip abductor activity has been previously investigated by the authors [38]. Activity in gluteus medius was increased by 16.5% compared to walking without aids when walking with TheraTogs (with cane use activity in gluteus medius was reduced by 22% compared to walking without aids). The increased activity with TheraTogs may be due to increased proprioceptive input provided by the orthosis or to the physical shortening of the muscle leading to increased overlap between the actin and myosin filaments and consequently a stronger contraction.

The authors hypothesize that cane use will inhibit activity on the hemiplegic side leading to reduced ipsilesional cortical activity and poorer long term functional gait outcomes. In contrast we hypothesize that TheraTogs will increase activity on the hemiplegic side during walking leading to increased ipsilesional cortical activity and improved long term functional gait outcomes.

We further hypothesize that cane use will inhibit the use of normal balance reactions leading to reduced balance recovery and poorer social participation. As no external support is provided with the TheraTogs orthosis the use of automatic balance responses will not be inhibited during walking. This will result in improved balance recovery and social participation.

The aim of this study is to investigate the long term effects of canes and TheraTogs on the recovery of motor control and co-ordination, gait, daily activity, balance and social participation when used in early gait rehabilitation following stroke.

## Methods - testing the hypothesis

### Design and setting

This study is a multi-centred single blind, randomised, control trial with parallel design.

Subjects will be recruited from the neurological rehabilitation department of 3 participating Swiss hospitals: Felix Platter Spital Basel, Kantonspital Luzern Neurorehabiltaton and Reha Clinic Zurzach. Each department is a dedicated unit specialising in the rehabilitation of post acute neurological patients. Ethical approval has been obtained from the following cantonal ethics committees: Basel (Ethikkommission Beider Basel), Luzern (Ethikkommission Kanton Luzern), Aargau (Ethikkommission Kanton Aargau).

### In- and exclusion criteria

All subjects (1) will be patients with hemiplegia following a first unilateral stroke, (2) will score at least level 3 on the Functional Ambulation Category (FAC) [39] (able to walk unaided on even ground but requiring verbal prompts and stand-by help without body contact) and (3) must have been independent walkers prior to insult without walking aids. (4) Subjects will have a Mini Mental State [40] score of 22 or above, (5) will have no orthopaedic or other neurological conditions that could limit walking ability, (6) have no gross visuospatial or visual field deficits and (7) will have no medical contraindications to walking.

### Recruitment

Potential subjects will be identified by rehabilitation staff at the participating hospitals. Suitability for participation will be checked and confirmed by the researchers. Signed, informed consent will be obtained from subjects before inclusion and randomisation. Subjects will be randomised into TheraTogs (intervention) and cane (control) group (see below). Intervention will begin when patients have reached level 3 on the FAC.

### Intervention details

Interventions will be applied for five weeks. If patients become independent walkers before this time (FAC 5) the intervention will be discontinued. If patients are discharged before this time and have not reached FAC 5 where possible the home carer will be instructed in the application of TheraTogs and the intervention will continue for 5 weeks as planned. TheraTogs will be applied as part of the washing/dressing routine in the morning by therapists or nursing staff instructed in the standard application. Subjects will walk throughout the day until preparing for bed with the prescribed walking aid. Standby assistance only will be provided during walking when necessary for safety. No other form of walking aid will be used for the duration of the study intervention. Foot or foot/ankle orthoses will remain unchanged and be worn as usual. All other forms of therapy (frequency and type) will remain unchanged and documented. Patients will receive usual care. When therapists feel that TheraTogs hinders treatment sessions the application may be removed for the duration of the session. It must be immediately reapplied with the standard application following treatment. When necessary TheraTogs may be removed for sleeping in the afternoon. It will be reapplied with the standard application on waking.

TheraTogs is worn directly on the skin. Attached to the basic suit hip abductor support [38] will consist of two broad straps attached 1.to the anterior torso, pulled downwards across the abductors towards and attached to the posterior aspect of the hemiplegic leg and, 2. to the posterior aspect of the torso pulled downwards to cross the abductors and attach to the anterior aspect of the hemiplegic leg. For hip extension one wide strap will be attached to the top of the pelvic rim on the non-hemiplegic side, pulled downwards and laterally passing across the buttock and towards the anterior aspect of the hemiplegic thigh attaching laterally (Figure 1.). Standard application training sessions will be provided to all staff before study begin. Written and photographic instructions will be provided. TheraTogs suits will be marked to ensure consistent application.

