**Figure 1 F1:**
[figure not shown]
**Standard Application TheraTogs**.

In the control group cane walking will take place with cane held at the level of the radial styloid of the sound wrist. Occurrences of non-adherence to the protocol will be documented in subject notebooks.

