### Measures

Outcome measures will be taken at baseline, defined as the day before intervention begin, the day after intervention is completed (max. 5 weeks), 3 months, 6 months and 2 years after intervention begin.

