### Sample size and power calculation

In order to detect a clinically significant difference in the primary outcome measure of "Timed up and go" of 10 sec (from a likely range of 10-40 sec), with a probability of 80% at a two sided 5% significance level a total of 116 patients (58 per group) must enter the study. This calculation was performed assuming a SD of the timed up and go of 19 sec [52]. Since there are indications that the distributions of the primary endpoint variable is skewed, the use of a nonparametric test should increase the actual power. To allow for drop-outs 60 participants per intervention will be recruited.

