### Statistical methods

The primary analysis will be performed in an intention-to-treat fashion, i.e. all subjects who where randomised and have at least a Timed Up and Go assessment before start of therapy will be included in all analyses. In the primary analysis, missing values will be replaced by the last available value. If no value under or after treatment is available, the value measured before start of therapy will be used.

The primary analysis will be performed on the Timed Up and Go after 5 weeks of therapy. A nonparametric two sample Wilcoxon-Mann-Whitney test will be performed. Significance levels will be 5%. As robustness analyses, an analysis of covariance will be performed with the value before start of therapy as covariate and centre and therapy as factors. 95% CI's will be calculated based on this analysis. Descriptive statistics for all data will be presented. For continuous data, this will include the change from pre-therapy values. Pre-therapy values will be compared between groups to identify relevant co-variables.

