## Discussion - implications of the hypothesis

Various forms of walking aids are commonly used in post stroke rehabilitation although the long term effects have been sparsely researched. In order to ensure the positive effect of these treatments and to enable evidence based practice, these interventions should be clinically researched.

Early walking is an important aim of stroke rehabilitation for many reasons including the psychological well-being of the patient, to prevent loss of cardiovascular fitness or the development of secondary musculoskeletal problems. This study questions whether canes are the optimal walking aid to enable early independent walking as their use inhibits rather than stimulates activity of the hemiplegic musculature and reduces the use of automatic balance responses contrary to the aims of rehabilitation. A possible alternative to cane use was recently tested by the authors in whom the immediate effects of TheraTogs were to significantly improve hip abductor muscle activity compared to cane walking or walking without walking aids [38].

The rate of recovery of all impairments after stroke is greatest in the first few weeks and slows down after two to three months. Kwakkel et al. discussed an early window during which rehabilitation has the most long term impact [17]. The potential negative or positive effects of walking aids may therefore be particularly significant in this early stage. To our knowledge no studies have investigated this question before. The results of this study may have important clinical significance and could be used in the development of guidelines for gait rehabilitation following stroke.

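### The primary Timed Up and Go is analysed as a five-week value but scheduled at the end of the intervention, so patients who reach FAC 5 early are tested early

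*Protocol article*

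**What the plan says.** - **Analysis time point** (Protocol article, Statistical methods): "The primary analysis will be performed on the Timed Up and Go after 5 weeks of therapy".
- **Visit schedule** (Measures): after baseline, tests fall on "the day after intervention is completed (max. 5 weeks), 3 months, 6 months and 2 years after intervention begin". The first of these follows the end of the intervention and has five weeks only as an upper limit. The later ones are counted from the start.
- **Early stop** (Intervention details; the Abstract agrees): "If patients become independent walkers before this time (FAC 5) the intervention will be discontinued". The rule is the same for both arms.
- **Discharge below FAC 5** (Intervention details): "where possible the home carer will be instructed in the application of TheraTogs and the intervention will continue for 5 weeks as planned". The sentence names TheraTogs only.
- **Cane arm** (Intervention details, after Figure 1): "In the control group cane walking will take place with cane held at the level of the radial styloid of the sound wrist". No carer condition is attached.
- **Recovery over time** (Discussion): "The rate of recovery of all impairments after stroke is greatest in the first few weeks and slows down after two to three months".

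**The concern.** A primary endpoint needs one time point, and the article gives two that agree only for patients who complete the full five weeks. For the others, the test date depends on when they reach FAC 5. That is functional recovery after randomisation, and the trial's hypothesis is that the aid changes it.

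If recovery is still under way, an earlier TUG tends to be slower than the same patient's TUG at week 5 would have been. An arm whose patients reach FAC 5 sooner is then measured at an earlier point on its recovery curve, so its advantage tends to shrink. A rule common to both arms does not guarantee common timing when the event that triggers it can differ by arm. At stake is whether the primary comparison describes both arms at the same time after the start of treatment.

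**Working it through.** **1. The two statements applied to one patient.** Take a patient in either arm who reaches FAC 5 at the end of week 2.
- Under Intervention details, the intervention stops.
- Under Measures, the test is the next day. The following test is at 3 months.
- Under Statistical methods, the primary value is the one after five weeks' therapy. This patient has had two weeks' therapy and has no week-5 visit.
- If week 5 is treated as missing, the carry-forward rule in Statistical methods brings in the week-2 value. If the end-of-intervention test is simply taken as primary, it is the same week-2 value.

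So, on the written schedule, both readings lead to the same number. The difficulty is that this number is a week-2 value analysed beside week-5 values from other patients.

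**2. The discharge route.** A TheraTogs patient discharged below FAC 5 without an able carer may be unable to continue. If that counts as the end of the intervention, the Measures section brings the test forward. The document does not say that it counts, so this step is an inference.

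**3. The plan's own sample size.** Inputs from Sample size and power calculation: difference 10 s, SD 19 s ("This calculation was performed assuming a SD of the timed up and go of 19 sec"), two-sided 5%, power 80%.
- Normal approximation: n = 2 × (1.960 + 0.842)² × 19² / 10² = 56.7, so 57 per group.
- t-test version: 57.65, so 58 per group and 116 in total. This matches the plan, and the sample size is not in dispute.
- Standard error of the difference at 58 per group: 19 × √(2/58) = 3.53 s.
- Power: Φ(10/3.53 − 1.96) = 0.809.

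**4. Illustrative size.** Let p be the extra share of one arm tested early, w the weeks early and g the TUG improvement in seconds per week. All three are assumptions; the document gives none of them. The shift between arms is b = g × p × w. Power when b works against a true 10 s effect is Φ((10 − b)/3.53 − 1.96). The last column is the two-sided rejection rate when there is no true difference.

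| g (s/week) | p | w (weeks) | b (s) | b as % of SE | Power | Rejection rate, no effect |
|---|---|---|---|---|---|---|
| 0.5 | 0.10 | 1 | 0.05 | 1.4 | 0.805 | 0.050 |
| 1 | 0.10 | 2 | 0.2 | 5.7 | 0.793 | 0.050 |
| 2 | 0.10 | 2 | 0.4 | 11.3 | 0.777 | 0.051 |
| 2 | 0.10 | 3 | 0.6 | 17.0 | 0.759 | 0.053 |
| 2 | 0.30 | 3 | 1.8 | 51.0 | 0.642 | 0.080 |

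With 58 per group, p = 0.10 is about 6 patients and p = 0.30 about 17. If both arms have the same share tested equally early, p is zero and there is no average shift. The table works on means; the primary test is a Wilcoxon-Mann-Whitney test, so it is a yardstick only. It also gives early finishers the same weekly slope as everyone else, which nothing in the document supports.

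**The case against.** **End-of-treatment testing is a legitimate choice.** It measures patients straight after their own course of treatment, and a fixed date would catch FAC 5 stoppers after time off the aid. This stands as an argument about design. It does not reconcile the two sections: if end of treatment is meant, the time point in Statistical methods is mislabelled.

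**The article is condensed.** What happens to a discharged patient without a carer may well be in the full protocol. That weakens the discharge route. It does not touch the main point, which is a conflict between two statements in the article and not an omission.

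**The carer clause proves little.** A reader might infer that TheraTogs patients will be tested earlier than cane patients. The document does not support that. It never says that a patient without a carer has completed the intervention. Such a patient could equally be recorded as non-adherent and still be due at five weeks. The closing words of the clause can be read as covering both arms, and silence on the cane may mean only that a cane needs no training to apply. Entry at FAC 3 means "able to walk unaided on even ground but requiring verbal prompts and stand-by help without body contact", so a discharged cane patient may also need a helper.

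**Any bias could only work against TheraTogs.** A reader might infer this too. It could be argued for the carer route alone. If cane patients reached FAC 5 sooner, they would be tested earlier and the comparison would tend to favour TheraTogs.

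**The effect is small.** On the milder assumptions it is. The case rests on the conflicting time points and the low cost of removing them.

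**Conclusion.** The point holds as an inconsistency in the primary time point. It is a low-priority improvement. Statistical methods analyses a five-week value. Measures schedules an end-of-intervention value, and the FAC 5 rule makes the two differ for every patient who finishes early. The timing of the primary outcome therefore depends on recovery after randomisation.

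The effect on the result is conditional. It needs a difference between arms in how many patients reach FAC 5 early, or how early, and it needs TUG still to be improving over the weeks in question. The Discussion's statement on early recovery makes the second likely, but entry is set by reaching FAC 3 and not by time since stroke, so it is not certain. Given both, the faster arm's advantage tends to be understated. Which arm that would be, and by how much, cannot be settled from the document. The assumed scenarios shown give shifts from 0.05 to 1.8 s, or 0.5% to 18% of the 10 s target. The discharge route is secondary and inferred.

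**What to change.** Take the primary TUG at a fixed five weeks after the start of intervention in both arms, whether the patient stopped at FAC 5, stopped at discharge or completed the course. Use the same wording in Measures and Statistical methods. Record the stop date and any walking aid used between then and the test. No new rule is needed to keep patients in their randomised arm, since Statistical methods already includes all randomised patients with a baseline TUG.

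The cost is a few sentences. The change moves a visit without adding one and matches the later visits, which are already counted from the start of intervention. There are two downsides. FAC 5 stoppers would be measured after a period off the assigned aid, so the result describes a policy of using the aid until independent walking or five weeks. Some discharged patients would also have to be recalled at week 5, although they are already due back at 3 months.

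If the investigators prefer end-of-treatment testing, Statistical methods should name that as the primary time point and accept that it varies between patients.
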